### Methods for additional analyses {20b}

No additional analyses are planned for the study.

### Methods in analysis to handle protocol non-adherence and any statistical methods to handle missing data {20c}

Missing data are analyzed according to the intention-to-treat principles, i.e., analyzing individuals to their allocated groups regardless of, e.g., protocol non-adherence. Multiple imputations will be used to handle missing data.

### Plans to give access to the full protocol, participant-level data, and statistical code {31c}

The datasets analyzed during the current study and statistical code are available from the corresponding author on reasonable request, as is the full protocol.

### Composition of the coordinating center and trial steering committee {5d}

The Trial Steering Committee (TSC), which consists of representatives from the initiating and participating institutions, is the principal policy and decision-making committee of the trial and is responsible for the scientific conduct of the study.

### Responsibilities of TSC

YF, AD, and WH review the progress of study and necessary changes to the protocol to facilitate the smooth running of the study. The TSC will also ensure that the trial is conducted in accordance with the relevant principles and will provide overall supervision of the trial. All aspects of local organization (including recruitment, identifying potential recruits, obtaining consent, providing day to day support for the trial and medical responsibility of the patients) will be provided by the PI and YC. And the research coordinators (DL, FW, QH, WY, MZ, ZW, SS, SK, SC, SH, VY) will operate tDCS device, collect data, and follow-up the patients. The PI and the research coordinators meet weekly to oversee conduct and progress.

### Harms {22}

We record the possible side effects for each participant. Our trained team reports these data throughout the study using the serious adverse event reporting system. It is unlikely that the participants will be affected by a serious adverse event (SAEs) or a serious adverse reaction in this trial. Common adverse reactions include dizziness, headache, and scalp tingling. Only unexpected serious adverse events / reactions which are unrelated to these clinical procedures will be reported as SAEs. Additionally, Shanghai Mental Health Center has the insurance to cover all non-negligent harm associated with the protocol.

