### Objectives {7}

The primary objective of this study is to investigate the acute efficacy on suicidal ideation, measured by the Beck scale for Suicidal Ideation (BSI) score. We hypothesize that a higher efficacy and larger reduction in suicidal ideation will be observed in tDCS group than sham group after 1 and 2 weeks when tDCS performed as an adjunctive treatment.

The secondary objectives include:To investigate the acute improvement on other clinical measurements, measured by the 17-item Hamilton Depression Rating Scale (HAMD-17) score, etc., of duration-doubled tDCS or sham tDCS, after 1 and 2 weeks.To investigate the potential association among variation of WBC, CRP, NLR, MLR, PLR, NGF, BDNF, GDNF, IL, TNF-α, sTNFr1, sTNFr2 and suicidal ideation as well as depressive symptoms in MDD patients [11–13] treated by adjunctive tDCS.To investigate the clinical relevance of tDCS efficacy and side effect occurence.

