### Strategies to improve adherence to interventions {11c}

During the intervention, every session is completed by tDCS-CT devices (Neuroelectrics, Starstim 8, USA) conducted by Neuroelectrics’ software according to the result of randomization as group A or B. Sessions are recorded in one document, including starting and ending time, name of operator, adverse effect of each session. Process of each session was performed as the same.

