### Composition of the data monitoring committee, its role and reporting structure {21a}

A Data Monitoring Committee (DMC) has been established in the hospital to monitor study conduct, the safety, efficacy. The DMC is composed of clinicians independent of the study and statistician and independent from the sponsor and competing interests.

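### As written, serious events related to tDCS, and any serious event classed as expected, are not reported as SAEs

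*Protocol article*

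**What the plan says.** The rule on serious events is in the protocol article, Harms {22}: "Only unexpected serious adverse events / reactions which are unrelated to these clinical procedures will be reported as SAEs". It is the only rule for SAE reporting in the document.

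The same section opens with two broader statements: "We record the possible side effects for each participant", and then "Our trained team reports these data throughout the study using the serious adverse event reporting system". It also says: "It is unlikely that the participants will be affected by a serious adverse event (SAEs) or a serious adverse reaction in this trial". The reactions it names are mild: "Common adverse reactions include dizziness, headache, and scalp tingling".

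Other sections bear on harms:

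- Strategies to improve adherence {11c} describes a record of every session, "including starting and ending time, name of operator, adverse effect of each session".
- The Discussion says that side effects will be assessed regularly with scales and that this will be enough to pick them up.
- Objectives {7} lists as a secondary aim: "To investigate the clinical relevance of tDCS efficacy and side effect occurence". Secondary outcomes repeats this.
- The section on the data monitoring committee {21a} says that the committee "has been established in the hospital to monitor study conduct, the safety, efficacy".

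**The concern.** Relatedness and expectedness are normally recorded about a serious event once it has been counted. Here they decide whether it is counted. The direction is also the reverse of what safety reporting is for: the events kept are those judged not to come from the procedure, and those judged to come from it are left out.

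This matters in this trial for three reasons. The session length is 60 minutes, and the Discussion presents that duration as intensive and unique among studies in this disorder, so serious harm from the device is a question the trial should be able to answer. All participants enter with suicidal ideation (BSI of at least 6) and a HAMD-17 score of at least 17, so serious suicidal events can be foreseen. And the Discussion concedes that this kind of sham may be told apart from active stimulation. If blinding leaks, relatedness may be judged differently in the two arms, and a rule that drops related events would then remove more events from the active arm.

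**Working it through.** The protocol gives no figure on this point, so there is nothing to reproduce. The check applies the rule literally and compares it with the other statements on harms.

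**Step 1. The conditions.** The Harms sentence sets three conditions that must all be met: serious, unexpected, unrelated to the clinical procedures. Its opening word makes them exclusive.

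**Step 2. The four classes of serious event.**

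| Relatedness | Expectedness | Reported as SAE? |
|---|---|---|
| Unrelated | Unexpected | Yes |
| Unrelated | Expected | No |
| Related | Unexpected | No |
| Related | Expected | No |

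One class of four is reported. Both related classes are lost.

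**Step 3. Effect on the comparison of arms.** Let U and R stand for unrelated and related, and u and e for unexpected and expected. The true number of serious events in an arm is Uu + Ue + Ru + Re. The number reported as SAEs is Uu. The arm difference in reported SAEs is Uu(active) − Uu(sham). The terms Ru and Re, which carry any serious harm judged to be caused by the device, do not enter it, however large they are.

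**Step 4. Where a suicidal event falls.** The protocol does not list expected events. A suicide attempt judged unexpected and unrelated is in the first row and is reported. The same attempt judged expected, on the ground that suicidal ideation is an entry criterion, is not. Nor is it reported if judged related. The text leaves the answer to the person classifying it.

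**Step 5. Consistency within the document.**

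- In ordinary usage an adverse reaction is an event thought to be caused by the intervention. A serious reaction that is unrelated to the procedure is therefore an empty category, so the rule contradicts itself.
- Two sentences in the same section say that side effects are recorded for each participant and reported through the SAE system. The rule then excludes related serious events from being reported as SAEs. Both cannot be followed for a serious side effect.
- The Discussion's assurance that side effects are sufficiently captured does not hold for SAE reporting under this rule.

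**Step 6. Does another section restore the lost events as SAEs?** None does. The session record covers the ten sessions, which fill the first 2 weeks, while assessment runs to week 8, that is 8 − 2 = 6 further weeks. A suicide attempt or an admission between visits is not naturally an adverse effect of a session. The side-effect scales may pick up some events, but nothing says that they are then handled as SAEs.

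**The case against.** The strongest reply is that the sentence governs only what is labelled an SAE. Side effects are recorded for each participant and each session, scales are used regularly, and side-effect occurrence is a secondary outcome. Criteria for discontinuing {11b} makes a serious physical disease a reason to stop whether or not it is related to tDCS, so such a case would be noticed. Retention {18b} provides for outcome collection after discontinuation. All of this stands, and it limits the point. Four stronger readings that a reader might infer are not supported:

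- *Related serious events vanish from the safety data altogether.* They are lost from SAE reporting. They could still appear as side effects without the SAE label.
- *Suicidal events are excluded.* This is conditional. The protocol does not class them as expected, names only dizziness, headache and scalp tingling as common reactions, and calls any serious event unlikely. Foreseeable is not the same as expected in the reporting sense.
- *The DMC sees only this reduced stream.* The committee has a safety role, but its data feed is not defined and is not limited to SAEs.
- *Side effects cannot be compared by arm.* They can, from the per-participant and per-session records. The secondary objective does not mention SAEs.

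It can also be said that the sentence is a slip for the word related, and its internal contradiction makes that plausible. The text does not say so, however, and staff would apply it as printed. Changing that one word would not be enough: the rule would then report one class of four again (related and unexpected), and every serious event judged unrelated or expected would stay outside.

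**Conclusion.** The rule is wrong as written; this is not detail left out for brevity. Followed literally, it reports one of four classes of serious event as SAEs and leaves out every serious event related to tDCS and every one classed as expected, possibly including suicidal events. SAE counts by arm would omit serious harm caused by the device, even though side effects are recorded elsewhere. No number of affected events can be given, because the document states no event rates.

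The conclusion on related events rests only on the literal wording. The conclusion on suicidal events assumes in addition that some would be judged expected or related. A difference in bias between the arms assumes that relatedness is judged differently in them, for instance if blinding fails. The sentence should be corrected, and the Harms section and the Discussion reconciled with it.

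**What to change.** Replace the sentence in Harms {22} with wording such as:

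> All serious adverse events from randomisation to week 8 are recorded and reported as SAEs, whatever their relatedness or expectedness, including suicide attempts, hospitalisation for suicidality and death. Relatedness and expectedness are recorded by blinded staff as attributes, not filters. SAEs are tabulated by arm and sent to the DMC.

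Starting at randomisation, not at the first session, matches the intention-to-treat analysis and covers events that occur before stimulation begins. The statement on reporting side effects through the SAE system should be reworded so that it fits the new rule.

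The cost is a wording change and slightly more reporting work. Sample size, eligibility and treatment are unaffected. The article describes the trial as still enrolling, and its section on amendments {25} provides a route for the change. Serious events already classified under the present sentence would need to be reviewed again.

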### Auditing {23}

The Ethics committee of Shanghai Mental Health Center at Shanghai Jiao Tong University will continue to review the trial. The TSC will check consent forms, compliance with the protocol and the planned tDCS interventions, and the quality of data collected in the case report forms at least annually.

### Plans for communicating important protocol amendments to relevant parties {25}

All changes will be communicated to sponsors and other relevant parties. In addition, deviations from the published protocol will be documented in the trial registration on ClinicalTrials.gov (Unique Protocol ID: 2021-YJXYS-06). Important amendments will be communicated to participants and reconsent obtained where appropriate.

## Patient public involvement

No public or patient involvement in the design of the protocol.

### Dissemination plans {31a}

Incidences from negligence (e.g., major protocol violations) will not be covered by study insurance. The PI will review all publications and be considered for lead author derived from this study. No later than 5 years after the ending of recruitment, we will deliver the whole deidentified data set to an appropriate data archive. All the results obtained from the present research will be published in some articles.

## Discussion

In this double-blinded, randomized, sham-controlled trial, we aim to determine the acute effectiveness of duration-doubled tDCS on suicidal ideation in patients with MDD. In addition to their usual treatment, participants will be randomly assigned to receive either 10 weekday sessions of active (2 mA) or sham tDCS as an adjunctive treatment, with the anode over the left DLPFC and the cathode over the right DLPFC. We will regularly assess suicidal ideation, depression severity, and functional impact using the BSI, HAMD-17, MADRS, ODQ, YMRS, CGI, and SDS throughout the trial. We will assess cognitive changes using WCST and SCWT, and also regularly assess treatment-related side effects using validated scales.

As suicidal ideation is regarded as one of the most important component in depression, the study will examine how suicidal ideation and depression change in participants with MDD throughout the trial period. Entrance and exit interviews will be recorded and analyzed by staffs in this research team in Shanghai Mental Health Center.

The study has numerous strengths and will follow the CONSORT (Consolidated Standards of Reporting Trials) 2010 statement on design and reporting [24]. Using REDCap to randomly assign participants to treatment groups will ensure that allocation is truly concealed, documented, and unchangeable. To minimize the placebo effect, both participants and treating investigators will be blinded. Primary and secondary outcomes were chosen to capture a range of subjective, objective, and functional measurements of suicidal ideation, depression severity, and the regular use of adverse event scales will ensure that treatment side effects are also adequately captured. Measurements will also be taken at multiple points during and after the trial to better describe the overall course and persistence of any treatment-related effects.

This study is unique for several reasons. It is the first of its kind to examine a MDD population with suicidal ideation, in which participants will have suffered from this mental disorder. The use of a relatively intensive tDCS regimen, in terms of session duration, is also unique among studies conducted with MDD. To our knowledge, this is also the first tDCS study for MDD that includes detailed measures of suicidal ideation. This may be useful in revealing the effect of this duration-doubled tDCS on suicidal ideation and in building a database of anonymized recordings for use in future analyses.

This study also has several practical limitations that may affect the results. With regard to treatment modality, delivering tDCS in a hospital setting will impose a minimal burden on inpatients, but outpatients will have to be functional enough to arrange for transport to the hospital on a daily basis. As such, there is a risk that the study population may miss outpatients with severe depression. The need for daily travel to the hospital can also pose problems with participant compliance. We may use home-based tDCS in future studies to mitigate this, although funding limitations prevented us from employing this approach in this trial. Second, our blinding procedure follows that used in most other studies of tDCS, but recent evidence suggests that this may not sufficiently mitigate the placebo effect. Turi et al. [25] showed that healthy volunteers were able to distinguish the fade-in, short stimulation, fade-out method of sham stimulation, described above, from true active stimulation at a level significantly greater than chance. It is not yet known how generalizable these findings are to a population with depression, but there is a need for more research into alternative methods of blinding in tDCS studies.

## Conclusions

In conclusion, this trial is a pragmatic, randomized, double-blinded, and sham-controlled study that seeks to compare the impact of active versus sham duration-doubled tDCS in treating MDD patients with suicidal ideation. To our knowledge, this study is the first of its kind in this patient population and also the first to conjointly employ detailed measures of suicidal ideation, which will also be used in future analyses. Given the immense health, economic, and societal impacts of MDD, new and effective treatments beyond pharmacotherapy and psychotherapy are needed, and tDCS may prove useful in this regard.

### Trial status

This trial is in the enrolment stage. The protocol was registered with ClinicalTrials.gov under protocol registration number NCT05555927 on September 25, 2022. Recruitment began on October 10, 2022. Recruitment is expected to be completed in March 2024.

## Abbreviations

BDNF: Brain-derived neurotrophic factor
BSI: Beck Scale for Suicide Ideation
CGI: Clinical Global Impression Scale
CONSORT: Consolidated Standards of Reporting Trials
CRP: C-reactive protein
DLPFC: Dorsolateral prefrontal cortex
DMC: Data Monitoring Committee
DSM-5: Diagnostic and Statistical Manual of Mental Disorders, Fifth Edition
GDNF: Glial-cell line derived neurotrophic factor
HAMD-17: 17-item Hamilton Depression Rating Scale
MADRS: Montgomery–Asberg Depression Rating Scale
MECT: Modified electroconvulsive therapy
MLR: Monocyte-to-lymphocyte ratio
IL: Interleukins
MDD: Major depressive disorder
MINI: Mini-International Neuropsychiatric Interview
NGF: Nerve growth factor
NLR: Neutrophil-to-lymphocyte ratio
ODQ: Oxford Depression Questionnaire
PI: Principal investigator
PLR: Platelet-to-lymphocyte ratio
RCTs: Randomized clinical trials
rTMS: Repetitive transcranial magnetic stimulation
sTNFr1: Soluble tumor necrosis factor receptor 1
sTNFr2: Soluble tumor necrosis factor receptor 2
t_1_: After 5 sessions
t_2_: After 10 sessions
t_3_: At the end of 4 weeks
t_4_: At the end of 6 weeks
t_5_: At the end of 8 weeks
t_6_: At the end of 12 weeks
tDCS: Transcranial direct current stimulation
TNF-α: Tumor necrosis factor-alpha
TSC: Trial Steering Committee
SAEs: Serious adverse events
SCWT: Stroop color–word test
SD: Standart deviation
SDS: Sheehan Disability Scale
WBC: White blood cell
WCST: Wisconsin card sorting test
YMRS: Young Mania Rating Scale
